### Methods in analysis to handle protocol non-adherence and any statistical methods to handle missing data {20c}

We want to ensure the treatment effect is not conservative; therefore a modified-to-treat approach will be used in the analysis of this trial. To be included in the analysis, participants will need to take the intervention for 75% of the 28 days pre-ST and for 75% of the 70 days post-ST. The study protocol is designed to maximize data collection. Missing data for secondary outcomes, particularly dietary intakes, the statistical method of multiple imputation will be used.

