**Fig. 2 Fig2:**
[figure not shown]
Study design flowchart

The visits and timeline is described below:
Visit 0 (virtual visit): Eligibility screening and informed consent will follow if the participant meets the criteria.Visit I (initial consult): Informed consent (if not given virtually at Visit 0). Randomization to either inulin or placebo group. Baseline periodontal assessment (PD and BOP), anthropometry (weight, height), dietary assessment, salivary markers of inflammation, and periodontal-associated pathogensVisit II (ST is performed): Anthropometry (weight, height), dietary assessment, salivary markers of inflammation, and periodontal-associated pathogens. ST is typically scheduled 4 weeks from the patient’s initial consultation.Visit III (follow-up, post-ST): Final periodontal assessment (PD and BOP), anthropometry (weight, height), dietary assessment, salivary markers of inflammation, and periodontal-associated pathogens.

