### Eligibility criteria {10}

Inclusion criteria include patients of both sexes, attending the clinic with a diagnosed periodontal disease requiring ST and over the age of 19 who are willing and able to provide informed consent.

Exclusion criteria included pregnancy, breast-feeding, demonstrating glycated hemoglobin (HbA1c) levels greater than 8% in the previous 3 months, chronic GI conditions (e.g., colon cancer, inflammatory bowel disease, celiac disease) and infections, use of antibiotics for the management of non-periodontal conditions within the previous 4 weeks, individuals who cannot stop taking laxatives, prebiotics, probiotics, and/or fiber supplements 2 weeks prior to the start of the intervention and for the duration of the study and current smoking and/or cannabis use. Patients with severe periodontal disease that require antibiotics with ST as part of their treatment will be withdrawn. This will be determined after the patients’ initial consultation (Visit I). Patients will also be withdrawn if they do not come back for Visit II or III. The eligibility criteria are summarized in Table 1.

**Table 1 Tab1:** Participant inclusion, exclusion and withdrawal criteria

Inclusion criteria	Exclusion criteria	Withdrawal criteria
· Patients of both sexes attending the clinic with periodontal disease · Over the age 19 (no upper age restriction) · Be able to provide informed, written, or verbal consent	· Demonstrating HbA1c levels greater than 8% in the previous 3 months · Chronic GI conditions (e.g., colon cancer, inflammatory bowel disease, celiac disease) and infections · Current or previous use of antibiotics for management of non-periodontal conditions within the past 4 weeks · Individuals who cannot stop taking laxatives, prebiotics, probiotics and/or fiber supplements 2 weeks prior to the start of the intervention and for the duration of the study · Smokers and/or cannabis users · Pregnant or lactating	· Patients with severe periodontal disease that require antibiotics with ST as part of their treatment · Patients who do not show for Visit II or Visit III

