### Criteria for discontinuing or modifying allocated interventions {11b}

Inulin administered at 10 g/day is generally well-tolerated, resulting in only mild gastrointestinal (GI) symptoms of gas/bloating, flatulence, constipation, and GI cramping/rumbling [25]. Furthermore, participants will be instructed to divide the 10 g dose into two 5 g doses—in the morning and evening. This method has been shown to have no significant increase in GI symptom incidence [26]. We believe this will minimize, if any, side effects from the intervention. If the participant cannot continue with the study for any reason, they will be aware they may stop the intervention at any time and it will not affect the level of care they receive at the clinic.

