### Strategies to improve adherence to interventions {11c}

All participants will receive exactly 100 sachets to last them until their scheduled follow-up appointment. They will be asked to return any unused sachets when they come in for their follow-up to account for missed dosages. Participants will receive a daily reminder to take the prebiotic in the morning and afternoon using an online application (Auto Message) and will also be instructed to take it prior to brushing their teeth in the morning and at night as an additional reminder.

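### The only analysis set described is selected on adherence after randomisation, with no analysis of all randomised participants stated; one final sachet count cannot always settle who belongs in it

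*Protocol article*

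**What the plan says.** Section {20c} of the protocol article gives one analysis set and the reason for it: "We want to ensure the treatment effect is not conservative; therefore a modified-to-treat approach will be used in the analysis of this trial". To be analysed, "participants will need to take the intervention for 75% of the 28 days pre-ST and for 75% of the 70 days post-ST". No second set is named there or elsewhere in the article, not even as a sensitivity analysis. The same section limits its missing-data method: "Missing data for secondary outcomes, particularly dietary intakes, the statistical method of multiple imputation will be used". Nothing is named for missing probing-depth or bleeding outcomes.

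Timing matters here. The visit list under Trial design {8} places "Randomization to either inulin or placebo group" at Visit I, before any product is taken. Eligibility criteria {10} adds two withdrawals: patients found after the Visit I consultation to need antibiotics with sanative therapy (ST), and patients who miss Visit II or III.

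On measuring adherence, section {11c} says "All participants will receive exactly 100 sachets to last them until their scheduled follow-up appointment" and "They will be asked to return any unused sachets when they come in for their follow-up to account for missed dosages". The Visit II entry in the visit list covers anthropometry, diet, saliva and pathogens, with no sachet count.

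**The concern.** In a superiority trial, analysing everyone as allocated keeps the comparison between groups that differ only by chance and by treatment. Under section {20c}, membership depends on behaviour during treatment. The stated motive, avoiding a conservative effect, gives up the protection that an as-randomised analysis provides when some participants do not adhere.

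Two features make a problem plausible, though not certain. Section {11b} describes inulin as "resulting in only mild gastrointestinal (GI) symptoms of gas/bloating, flatulence, constipation, and GI cramping/rumbling", so tolerability could affect intake more in one arm. Section {11c} ties the supplement to tooth-brushing, so people who take it regularly may also clean their teeth more regularly. If those who drop below 75% differ between arms in their expected healing, part of any observed difference would come from selection. With no all-randomised result planned, a reader could not tell how much.

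The rule also needs intake in two separate periods, while the article describes one count at the end.

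**Working it through.** **Inputs from the protocol.** Mean changes of 81 and 91 sites, SD 21, 80% power, alpha 0.05, 71 per group, 20% drop-out, 85 per group (Sample size {14}); periods of 28 and 70 days with a 75% threshold ({20c}); 100 sachets, returned once ({11c}). The protocol gives no adherence rate and no link between adherence and outcome, so both are assumed below.

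**1. The plan's own figure.** Standardised difference = (91 − 81)/21 = 0.476. A two-sided t test at 0.05 with 80% power needs 70.2, so 71 per group, which reproduces the plan (the sides are not stated; two-sided fits). The 85 corresponds to 71 × 1.2 = 85.2. A 20% loss from 85 leaves 85 × 0.8 = 68 per group, with power 78.7%.

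**2. Bias from selecting on adherence, with no true effect.** Let adherence be a standard normal score with correlation r to site reduction, and exclude the lowest fraction q in each arm. The mean score of those kept is λ(q) = φ(z_q)/(1 − q), where z_q is the q quantile. Then

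bias = r × 21 × [λ(q inulin) − λ(q placebo)].

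λ(0.10) = 0.1950, λ(0.20) = 0.3500, λ(0.30) = 0.4967.

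- r = 0.1, 20% vs 10%: 0.1 × 21 × 0.1550 = 0.33 sites.
- r = 0.4, 30% vs 10%: 0.4 × 21 × 0.3017 = 2.53 sites, a quarter of the planned 10.
- Equal exclusion with the same r in both arms, or r = 0: zero.
- More exclusion on placebo, or a negative r: the sign reverses.

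A simulation of 4,000 null trials per setting, with 85 per arm before exclusion, agrees. At r = 0.3 and 30% vs 10%, the mean difference was 1.9 sites and the type I error 8.6%. At r = 0.3 and 20% vs 20%, the difference was 0.01 sites and the error about 5%.

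**3. Can one count apply the rule?** The thresholds are 0.75 × 28 = 21 days and 0.75 × 70 = 52.5, so 53 days. At one sachet a day:

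- the smallest total that can pass is 21 + 53 = 74;
- the largest total that can fail is 20 + 70 = 90.

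A total of 73 or fewer always fails and 91 or more always passes. Every total from 74 to 90 fits both outcomes. For example, 80 taken is a fail as 10 + 70 and a pass as 22 + 58. The undecided band is 10 to 26 sachets returned of 100, or 74/98 = 76% to 90/98 = 92% overall intake. The 28/70 split is itself nominal, since the visit list says only that ST is typically at four weeks.

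**4. Power under each approach.** As randomised, if 10% of the inulin group get no benefit, the difference becomes 0.9 × 10 = 9 sites and the standardised difference 9/21 = 0.429. Power is 79.3% with all 85 per arm measured and 69.9% with 68.

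Under the adherence set, if a further 10% are excluded from each arm after 20% drop-out, 68 × 0.9 = 61 per arm remain, with power 74% at the full 10 sites. At 20% further exclusion it is 54 per arm and 69%.

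**The case against.** The strongest reply is that allocation stays random and that bias is conditional. It needs exclusion that differs by arm, or selection that relates to both arm and outcome. Equal exclusion with the same selection leaves the type I error near 5%. Section {11b} also calls the dose generally well tolerated and says split dosing brings no significant increase in gastrointestinal symptoms, so the protocol gives no reason to expect a large arm difference in adherence. All of this stands, and it limits several stronger readings.

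- A reader might infer that randomisation is discarded. It is not; the compared groups are subsets of the randomised ones.
- A reader might infer that the rule favours inulin. That holds only if inulin loses more people and adherence goes with better healing, and the protocol establishes neither.
- A reader might infer that the 75% rule is unusable or that staff must guess. Totals outside 74–90 are decidable. The schedule of assessments (Table 2) is not visible in the text reviewed, so a Visit II count cannot be ruled out, and the article does not say who applies the rule. What can be said is that no Visit II count is described in the text available.
- A reader might infer that adherence exclusions fall outside the 20% allowance. The full-trial text calls it drop-out without defining it.

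The reply does not supply an all-randomised analysis. Nor is this a detail left to an analysis plan: {20c} makes and justifies the choice, and {31c} says the article presents the full protocol.

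**Conclusion.** The concern holds. Followed as written, the plan gives a per-protocol primary comparison in a superiority trial, with no stated as-randomised result beside it. This rests on the text of {20c} and on randomisation at Visit I, and needs no assumption.

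The size and direction of any bias cannot be known from the document. The range of about 0.3 to 2.5 sites depends on assumed exclusion of 20–30% vs 10% and an assumed correlation of 0.1–0.4. It is near zero under equal exclusion with the same selection in both arms. The case for change is that the primary result would rest on that unverified condition.

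The sachet point is secondary. From the single return described, inclusion is undecided for 74–90 sachets taken, assuming one sachet a day over 98 days.

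**What to change.** In section {20c}, define the primary analysis as all randomised participants in their allocated group, whatever their adherence. Then:

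- Collect the Visit III periodontal examination from participants who stop the supplement.
- Extend the multiple imputation already planned for secondary outcomes to missing probing-depth and bleeding outcomes.
- Reconcile the withdrawals in Eligibility criteria {10} (antibiotics with ST, missed visits) with this set, for example by keeping those participants' outcome data, or by settling the antibiotic question before randomisation. Recruitment {15} expects 10% of patients to need antibiotics, so this is not a marginal group.
- Keep the 75% rule as a labelled per-protocol sensitivity analysis, and add a sachet count at Visit II so that it can be applied.

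The cost is protocol wording, one count at an existing visit, follow-up of those who stop, and some dilution. The stated 80% power should be described accordingly: with 10% of the inulin group getting no benefit, about 79% if all 85 per arm are measured and about 70% with 68 evaluable. Restoring 80% under that assumption needs 87 evaluable per arm, or 87/0.8 = 109 randomised per arm at 20% drop-out. If the sample size stays at 170, the protocol should state the lower power.

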### Plans to give access to the full protocol, participant-level data, and statistical code {31c}

This study presents the full protocol. The datasets can be made available by the corresponding author when the trial concludes.

## Oversight and monitoring

### Composition of the coordinating center and trial steering committee {5d}

N/A—This is a single clinic trial involving a nutritional supplement.

### Composition of the data monitoring committee, its role and reporting structure {21a}

A data monitoring committee has not been established. This is a monocenter study design. The study results from the pilot study will be evaluated by the research team and may reveal suggestions for protocol amendments and/or a need for a data monitoring committee.

### Adverse event reporting and harms {22}

Hypersensitivity to inulin is extremely rare and mostly benign. We do not expect any adverse events to occur and participants can stop taking the intervention at any time.

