### Relevant concomitant care permitted or prohibited during the trial {11d}

All relevant concomitant care will be permitted and recorded.

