## Data collection and management

### Plans for assessment and collection of outcomes {18a}

Clinical data, including periodontal outcomes and anthropometric measurements, will be collected from electronic patient files and recorded in a specialized spreadsheet. This will be combined with data from the online dietary assessments and saliva analyses.

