### Plans to promote participant retention and complete follow-up {18b}

Participants regularly attend the appointments where we will be collecting data for their clinical care. Thus, we have designed the intervention around this schedule. As previously mentioned, side effects will be minimized by taking the intervention as two separate doses during the day. Also, we have minimized the burden on the participants by having the treatments individually packaged.

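### The harms section expects no adverse events although the protocol itself describes GI symptoms on inulin, and the visible text gives no way of recording symptoms or reasons for stopping

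*Protocol article*

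**What the plan says.** Section {11b} of the protocol article calls inulin at the trial dose generally well tolerated, "resulting in only mild gastrointestinal (GI) symptoms of gas/bloating, flatulence, constipation, and GI cramping/rumbling". It then describes dividing the daily amount, cites earlier work in which this did not significantly raise symptom incidence, and concludes: "We believe this will minimize, if any, side effects from the intervention". The retention section {18b} repeats that "side effects will be minimized by taking the intervention as two separate doses during the day".

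The section on adverse events and harms {22} has two sentences. One says hypersensitivity is very rare and mostly benign. The other reads "We do not expect any adverse events to occur and participants can stop taking the intervention at any time". The audit section {23} gives the absence of anticipated risk as its reason for not auditing.

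The visit list under Trial design {8} sets out the assessments at each visit. At Visit III they are "Final periodontal assessment (PD and BOP), anthropometry (weight, height), dietary assessment, salivary markers of inflammation, and periodontal-associated pathogens". On data sources, {18a} says "Clinical data, including periodontal outcomes and anthropometric measurements, will be collected from electronic patient files and recorded in a specialized spreadsheet", to be combined with the dietary and saliva data. Concomitant care is covered by one sentence in {11d}: "All relevant concomitant care will be permitted and recorded". Unused sachets are to be returned at follow-up {11c}.

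Under {20c}, a participant enters the analysis only after taking the product on 75% of the 28 days before sanative therapy (ST) and 75% of the 70 days after it. Section {31c} states: "This study presents the full protocol".

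**The concern.** A symptom attributed to the product is an adverse event even when it is mild. A protocol that describes such symptoms, and plans to limit them, should not also say in its harms section that no events are expected. The practical consequence is the greater worry: having expected nothing, the harms section goes on to describe no elicitation, recording or reporting.

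Two things are at stake. First, 14 weeks of daily supplementation in 170 people could end without a description of GI tolerability by arm, which anyone considering inulin as an adjunct to ST would want. Secondly, stopping the supplement removes a participant from the analysis set. If more participants fall out of one arm than the other, the reader will need to know whether intolerance was the reason, and the data described would not show it.

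**Working it through.** The claim rests on the text and not on a figure in the plan, so the check sets the sections side by side.

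**Step 1: do the statements agree?**
- {11b}: mild GI symptoms result at the trial dose; side effects are to be minimised.
- {18b}: side effects are to be minimised.
- {22}: no adverse events are expected.
- {23}: no risks are anticipated.

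The first pair treats side effects as something to manage. The second pair treats them as absent. They can be brought together only by reading {22} and {23} as referring to events of concern, and neither section says so.

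**Step 2: is collection described anywhere that can be seen?**
- Visit list in {8}: periodontal measures, anthropometry, diet, salivary markers and pathogens. No symptom or event item.
- Outcomes {12}: periodontal, salivary, microbial, anthropometric and dietary. No harm or tolerability outcome.
- Data collection {18a} and data management {19}: clinic file, dietary recall and saliva data only.
- Statistical methods {20a} and additional analyses {20b}: nothing on events.
- Harms {22}: no method.
- Table 2 under {13}: not shown, so it cannot be checked.

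**Step 3: what could still be reported by arm?** Withdrawals (no-shows at Visit II or III, or antibiotics with ST), the number of sachets returned, and concomitant care. A sachet count shows that doses were missed, not why. A withdrawal for antibiotics carries its own reason; a no-show or a decision to stop does not.

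**Step 4: how does this meet the analysis set?** The {20c} thresholds are:
- before ST: 0.75 × 28 = 21 days, so missing 8 or more days excludes;
- after ST: 0.75 × 70 = 52.5 days, so at least 53 days are needed, and missing 18 or more excludes.

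About a week of stopping before ST is therefore enough to leave the analysis. The sample size section {14} gives 71 needed and 85 recruited per group, an allowance of 85 − 71 = 14 per arm, or 28 of 170. Apart from antibiotic withdrawals, nothing visible would record why these participants were lost.

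**Step 5: would by-arm symptom counts be informative?** The protocol gives no symptom rates, so the rates here are assumptions. With 85 per arm and a common rate p, the 95% half-width for the difference between arms is 1.96 × √(2p(1 − p)/85):
- p = 10%: 9.0 percentage points;
- p = 30%: 13.8 percentage points;
- p = 50%: 15.0 percentage points.

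Power to detect 20% against 40% is about 82%, 30% against 50% about 76%, and 10% against 20% about 45%. The trial could describe a large difference in tolerability usefully and a small one only roughly.

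**The case against.** The strongest reply has four parts.

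*The schedule is unseen.* Table 2 is where an adverse event row would normally sit. This stands as a limit: the finding concerns the visible text. The visit list, outcomes and data sections give no sign of such a row.

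*The contradiction is soft.* Section {11b} says the product is generally well tolerated and that side effects will be minimised, if there are any. Section {22} may therefore mean only that nothing serious is expected. This is a fair reading of the intent, but {22} and {23} are worded without that limit, and {23} rests a decision on the wording.

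*An article condenses.* Case report forms are commonly left to fuller documents, and the sentence calling this the full protocol appears under data access. That sentence alone does not prove that no other document exists. However, the harms section is present and gives a reason for expecting nothing, so this is more than trimmed detail. A statistical analysis plan could not fill the gap, since it can only tabulate what has been collected.

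*The pilot may catch it.* Sections {21a} and {23} foresee a pilot review that could lead to amendments or a monitoring committee. Neither says that symptoms will be recorded, so on tolerability the review would have little to work from.

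A reader might also draw stronger conclusions, which the documents do not support:
- *The sponsor has decided not to record events.* The text never says so; it states no plan.
- *Nothing on tolerability could be reported by arm.* Withdrawals and sachet counts could be.
- *Symptom counts would show whether blinding held.* On their own they do not test that.
- *Collecting symptoms would cure the bias of the 75% rule.* It would help to explain unequal exclusions, not remove their effect.

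**Conclusion.** The point holds in a limited form. Sections {11b} and {18b} do not agree with {22} and {23}, and the visible text gives no means of asking about or reporting GI symptoms, adverse events or reasons for stopping. All 170 participants are affected as regards symptom data. For the efficacy comparison, the relevant group is those who stop or fall below 75% adherence; the plan's own loss allowance is 14 per arm, and exclusions for low adherence could add to it.

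No figure in the protocol measures how much this would distort the result, and none is claimed. The precision figures show only that the data would be worth having, under assumed symptom rates. The conclusion also assumes that Table 2 contains no adverse event row; if it does, what remains is the inconsistent wording and the lack of any stated reporting by arm. This should be corrected, but it does not by itself invalidate the primary comparison.

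**What to change.** 1. Reword {22} and {23} so that they agree with {11b} on what symptoms are expected.
2. State in {22}, and in the visit list, that a short fixed set of GI-symptom and adverse-event questions will be asked in the same words in both arms at Visits II and III. If Table 2 already has such a row, refer to it.
3. Record the reason whenever a participant stops the supplement or leaves the study. Visit questions will miss people who do not attend, but the team already e-mails or calls participants a week before Visits II and III {Dietary assessment}, and that contact could serve.
4. Report counts of symptoms, events and reasons for stopping by arm for all randomised participants who took any product, not only those who meet the 75% rule.

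The cost is a few minutes at two existing visits and one more descriptive table. No treatment, visit or sample size changes.
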